## Abstract

Women’s health concerns play a role in several of the UAE's major public health challenges, including cardiovascular disease, injuries, cancer, and respiratory conditions. The UAE's 2024 National Policy for improving Women’s health aims to lower cancer mortality rates to 23.24 per 100,000 females, with translational research projects utilizing bio-registries and biobanks supporting this goal. This article describes the protocol for the Dubai Women’s Health Study, a prospective cohort study aimed at investigating the feasibility of establishing a dedicated Women’s health biobank in Dubai to support translational research on improving Women’s health. Initial focus will be on polycystic ovarian syndrome (PCOS), endometriosis, pre-eclampsia, and endometrial cancer, which are prevalent health conditions in the UAE. Recruitment will start at the largest public Women’s hospital in Dubai (Latifa Women’s Hospital), with possible future inclusion of other private hospitals. The study will approach women diagnosed with PCOS, endometriosis, pre-eclampsia, and endometrial cancer over a 12-month period from April 2025 to April 2026, obtaining clinical details and biological samples for establishing a bio-registry and biobank. The feasibility will be evaluated based on recruitment rates, the willingness to contribute samples and logistical challenges. The biobank will support ongoing studies on endometrial cancer risk in PCOS and endometriosis, Co-enzyme A's role in pre-eclampsia, and genetic profiling of inherited endometrial cancer cases in Dubai. The study recruitment only commenced in July 2025 and there are no results yet. Aligned with the National Policy for Improving Women’s Health, the biobank provides a foundation for local and global Women’s health research, addressing historical gender neglect in medical research, and promoting health equity globally.

## Introduction

Women’s health is increasingly recognized as a global public health and development priority, closely aligned with the United Nations Sustainable Development Goals (SDG 3: Good Health and Well-Being and SDG 5: Gender Equality). The United Arab Emirates (UAE) is one of the fastest growing economies globally (1). Dubai, its international hub (2), is composed of a multi-cultural, multi-ethnic society and is home to over 200 nationalities (3). This diverse demography generates a wide range of genomes and phenotypes and a unique opportunity for researchers to study diseases. The UAE Vision 2031 (4) and the 2024 (5) National Policy for Improving Women’s Health emphasize innovation, precision medicine, biobanking, and data-driven policy to improve health outcomes.

On the 5th of February 2024, His Highness Sheikh Mohammed bin Rashid Al Maktoum, Vice President and Prime Minister of the UAE, and the Ruler of Dubai approved the National Policy for Improving Women’s Health in the UAE (5). The policy aims to develop a multisectoral national framework to promote Women’s health by providing high quality and efficient health services whether curative, preventive or rehabilitative. The policy specifically aims to reduce the cancer mortality rate from 70.3 to 23.24 and the all-cause mortality rate to 62.77 per 100,000 of the female population (6). Additionally, the policy's targets include reducing health issues arising from unhealthy lifestyles (e.g., lack of physical activity, poor diets, and obesity) by 3% (5). Implementing these agendas requires high-quality research across diverse Women’s health issues. Such research is essential for evidence-based policy and clinical decision-making. Women’s health issues contribute to some of the “Big 4” public health issues in the UAE (cardiovascular disease, injury, cancers, and respiratory diseases) (7). For example, women with polycystic ovary syndrome (PCOS) are at increased risk of cardiovascular disease, endometrial cancer (EC) (39), and asthma (8). Women who develop pre-eclampsia during pregnancy are at increased risk of cardiovascular disease in later life (9, 10) and women with endometriosis may also be at higher risk of breast and endometrial cancer (EC) (11). Of concern, is that there might be a higher prevalence of risk factors and Women’s health conditions in the UAE population compared to the global prevalence (12); however, population-based research is required to provide accurate and reliable estimates to make these comparisons and inform healthcare planning and expenditure in the UAE.

Recently, Dubai Health, the newly formed Academic Healthcare System, established a world-class biobank to support translational research. Dubai Health is Dubai's first integrated academic health system established to elevate the standard of care and to advance health for humanity. Dubai Health (13) is comprised of 6 hospitals, 26 ambulatory health centers and 21 medical fitness centers, Mohammed Bin Rashid University of Medicine and Health Sciences and Al Jalila Foundation. The mission is to serve patients through the integration of care, learning, discovery and giving. The family of 11,000 collaborates across multidisciplinary teams to put the patient first. Dubai Health Biobank is one of the largest in the country, having the capacity to store up to seven million biological samples. This provides a unique opportunity to support research into Women’s health in the UAE and provide collaboration opportunities with international researchers. Well-designed bio-registries and biobanks play a pivotal role in advancing health research. They enable longitudinal insights into disease risk, precision medicine, biomarker discovery, and epidemiology (14). This research infrastructure is therefore crucial to achieving the goals of the National Policy for Improving Women’s Health in the UAE.

Outside of Dubai, within the UAE, biobanking capacity has also expanded in recent years, with other initiatives such as the Abu Dhabi Biobank (15) providing high-quality biospecimen storage linked to clinical data. These platforms will support a wide range of biomedical research; however, they are largely population-based with no dedicated national biobank focused specifically on Women’s health conditions. Across the wider Gulf region, major population biobanks have been established, including the Qatar Biobank and the Saudi Biobank. These initiatives include substantial female participation. However, their primary focus remains general population health, genetics, and non-communicable diseases, with limited emphasis on women-specific conditions. A systematic review published in 2020 (16) identified 81 maternal and birth cohort studies from six Gulf Cooperation Council (GCC) countries (Bahrain, eight in Kuwait, seven in Qatar, six in Oman, 52 in Saudi Arabia, and seven in the UAE) primarily focused on correlation between maternal/reproductive and medical exposures, with birth and maternal outcomes. However, many studies were descriptive, underscoring the need for more robust long-term cohorts covering broader exposures. In the MENA region, Women’s health research is often conducted through disease-specific registries, hospital-based cohorts, or short-term studies rather than through dedicated, longitudinal Women’s health biobanks, and where a biobank is present, face challenges related to population level long-term biobank infrastructure (17). Globally, several large cohorts—including the Nurses' Health Study, the Women’s Health Initiative, the UK Biobank (18), and the All of Us Research Program (19)—have demonstrated the scientific value of linking biospecimens with longitudinal clinical data and enabling sex-stratified analyses. However, most global resources are not designed as dedicated Women’s health biobanks and predominantly reflect Western populations, underscoring the need for regionally anchored initiatives that address ethnic, genetic, and environmental diversity.

The Dubai Women’s Health Biobank aims to addresses these gaps by generating women-specific, ethnically diverse data, directly supporting SDG 3 (Good Health and Well-Being) and SDG 5 (Gender Equality). However, as establishing a biobank requires substantial infrastructure, governance, and stakeholder engagement, a feasibility study becomes a critical first step to determine operational viability. The International Society for Biological and Environmental Repositories (ISBER), (20) explicitly recommends that feasibility assessments precede implementation to determine the practicality of collection processes, infrastructure adequacy, staffing, and financial sustainability. It highlights how feasibility studies identify potential operational barriers early, support compliance with biospecimen quality standards, and ensure that planned collections align with scientific demand, thereby reducing risk and improving reproducibility. The United States National Cancer Institute also emphasizes the critical role of feasibility evaluation before establishing any biospecimen resource (21). It demonstrates how conducting feasibility analyses ensures that biobank objectives are realistic, ethically sound, and economically viable, while minimizing waste of resources and avoiding premature implementation of non-sustainable infrastructures. Finally, Soo et al. (22) describe the practical outcomes of performing a feasibility study before creating an academic biobank in a low-resource context and how early technical and financial assessments guided phased implementation, ensuring alignment between goals and capacity.

A feasibility study is more than planning. It safeguards scientific integrity, ensures ethical compliance, and supports financial accountability in biobank establishment. This article describes the protocol and progress so far with a study to investigate the feasibility of developing a dedicated Women’s health biobank in Dubai (UAE) to support research to improve Women’s health in the region. The objectives cover two areas. First, biobank operations: building data infrastructure, linking health records with samples, and measuring recruitment rates and willingness to contribute. Second, Women’s health conditions: collecting blood and stool samples to study EC risk in PCOS and endometriosis, the role of co-enzyme A in pre-eclampsia, and inherited EC cases in Dubai. The study also aims to evaluate logistical challenges (which is sample transportation, storage), measure financial sustainability for long-term projects, and identify the ethical and legal compliance requirements.

## Methods and analysis

### Study design

The Dubai Women’s Health Study will be a prospective cohort study in Dubai, UAE. The conditions of initial focus will include the following common and important Women’s health conditions in the UAE: PCOS, endometriosis, pre-eclampsia, and EC (Figure 1). Recruitment will start at Latifa Women’s Hospital in Dubai and may include other hospitals in the future. Latifa Women’s Hospital is part of Dubai Health, a public institution providing free or subsidized and accessible care to Emirati and non-Emirati citizens residents. This ensures broad socioeconomic representation. Latifa Hospital is a tertiary center that manages all four target conditions—PCOS, endometriosis, pre-eclampsia, and endometrial cancer—making it an ideal site for recruitment. The campaign will focus on key staff such as surgeons, specialists and nurses in obstetrics and gynaecology. Patient recruitment, sample collection and sample storage (Figure 2) are outlined below. The sample and data matrix are illustrated in Figures 3, 4. Figure 4 shows controlled biospecimen handling throughout its lifecycle to ensure high-quality, reliable samples for research. Figure 5 shows the workflow.

**Figure 1 F1:**
[figure not shown]
Women’s health conditions of initial focus in the dubai Women’s health biobank.

**Figure 2 F2:**
[figure not shown]
Study design. The Dubai Women’s Health Study will be a prospective cohort study in Dubai, United Arab Emirates.

**Figure 3 F3:**
[figure not shown]
Dubai Women’s health study sample and data matrix.

**Figure 4 F4:**
[figure not shown]
Controlled biospecimen handling throughout its lifecycle to ensure high-quality, reliable samples for research.

**Figure 5 F5:**
[figure not shown]
Workflow of the dubai Women’s health study.

### Participants

#### Inclusion criteria

The study aims to approach all women seen and given a diagnosis of endometriosis, PCOS, pre-eclampsia and EC over a 12-month period from April 2025 to April 2026 at Latifa Women’s hospital to seek consent to obtain clinical details and biological samples into the Biobank Information Management System (BIMS). Women approached will include all nationalities, be aged at least 18 years, resident in Dubai and able to provide informed consent. We will also aim to recruit women without endometriosis, PCOS, pre-eclampsia (pregnant women) and EC as controls. Control women for PCOS will be women with regular menstrual cycles identified from a gynecology or other appropriate outpatient setting. Control women for endometriosis and EC will be women undergoing gynecological surgery for benign conditions other than endometriosis or EC. Control women for pre-eclampsia will be normotensive pregnant women matched for approximate weight, age (5-year age group), and week of gestation.

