#### Exclusion criteria

The study will exclude the following women. Non-residents in Dubai as they are less likely to be available for long-term follow-up, pregnancy (for the PCOS, endometriosis and EC aspects), younger than 18 years, and those unable to provide consent.

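### EC controls share the endometriosis-control rule, so they are depleted of endometriosis and unsuited to estimating the endometriosis–EC association

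*Protocol article*

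**What the plan says.** Under Inclusion criteria, a general sentence introduces the controls: "We will also aim to recruit women without endometriosis, PCOS, pre-eclampsia (pregnant women) and EC as controls". Condition-specific rules follow. Endometriosis and EC share one: "Control women for endometriosis and EC will be women undergoing gynecological surgery for benign conditions other than endometriosis or EC". It does not mention PCOS.

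Cases are taken without regard to coexisting conditions: "The study aims to approach all women seen and given a diagnosis of endometriosis, PCOS, pre-eclampsia and EC over a 12-month period". Apart from non-residents, Exclusion criteria lists only "pregnancy (for the PCOS, endometriosis and EC aspects), younger than 18 years, and those unable to provide consent". Nothing there bars an EC case who has endometriosis or PCOS.

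The scientific use is stated twice. The Abstract says "The biobank will support ongoing studies on endometrial cancer risk in PCOS and endometriosis", and the objectives at the end of the Introduction include "collecting blood and stool samples to study EC risk in PCOS and endometriosis". Sample size plans 30 women with EC and a matching number of age-matched controls. Outcome measures counts having enough samples for the baseline studies as one of the feasibility outcomes.

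**The concern.** In a case-control comparison, controls should show how common the exposure is in the population that produced the cases. Here endometriosis is both the index disease of one arm and a candidate exposure for another arm's outcome. Screening it out is right for the endometriosis controls. For the EC controls it removes exposed women from one side only.

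The question at risk is the endometriosis–EC association. The feasibility outcomes could count 30 EC controls as sufficient for a baseline study that those controls cannot support. Adjustment cannot repair this, because exposed women who were never sampled as controls cannot be recovered. Dropping the exposed cases to restore balance would remove the question itself. Recruitment began in July 2025, so controls may already be accruing under this rule.

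**Working it through.** **The plan's own figure.** The only precision figure is ±10% for a 50% participation rate with 100 women (Sample size). Check: 1.96 × √(0.5 × 0.5 / 100) = 0.098, or 9.8 percentage points. It reproduces, and the control rule has no bearing on it. The article gives no figure for an EC comparison.

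**Inputs.** From the documents: 30 EC cases and about 30 controls. Assumed, because the documents give neither: the prevalence p of endometriosis in the source population (5%, 10%, 20%), and the share f of exposed women that the rule removes from the controls (0 to 1). Controls are otherwise taken as representative of the source population.

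**Direction and size.** Exposure odds in cases are OR_true × p/(1 − p). Exposure odds in controls are p(1 − f)/(1 − p). Dividing,

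OR_observed = OR_true / (1 − f),

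which does not depend on p. With OR_true = 1:

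| f | Observed OR |
|---|---|
| 0 (controls drawn regardless of endometriosis) | 1.0 |
| 0.5 | 2.0 |
| 0.9 | 10.0 |
| 1 | not estimable (no exposed controls) |

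The shift is always upward, which is not always away from the null: a true OR of 0.5 with f = 0.5 gives 0.5/0.5 = 1.0.

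**Extreme case at the planned size (f = 1, OR_true = 1).** Adding 0.5 to each cell, with a exposed cases of 30 and 0 exposed controls of 30, OR = [(a + 0.5)/(30 − a + 0.5)] / (0.5/30.5):

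| Assumed p | Exposed cases a | Corrected OR | Fisher p |
|---|---|---|---|
| 5% | 2 (1.5 rounded up) | 5.35 | 0.49 |
| 10% | 3 | 7.76 | 0.24 |
| 20% | 6 | 16.18 | 0.024 |

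These ORs depend on the 0.5 correction and the assumed prevalence, so they illustrate the problem and do not predict a result. Random error is large at 30 per group. The systematic shift would remain in a larger study using the same rule.

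**Spill-over to another factor X.** At f = 1, the spurious OR for X is the odds of X in the whole source population divided by its odds in women without endometriosis. For p of 5% to 20%, and X present in 10% or 30% of women without endometriosis:

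- X unrelated to endometriosis: 1.00.
- X–endometriosis OR of 2: 1.04 to 1.19.
- X–endometriosis OR of 0.5: 0.89 to 0.97.

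Unrelated factors are unbiased. Related ones move modestly under these assumptions, in either direction.

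**The case against.** The strongest reply is that no such analysis is planned. Study design calls this a prospective cohort, the outcomes concern feasibility, and no EC odds ratio is specified. Studying EC risk in these women can mean following women with PCOS or endometriosis against their own controls, where absence of the exposure is correct. This stands as a limit: the defect lies in the resource and not in a planned estimate. It does not dispose of the point. Follow-up is only a possibility (Follow-up collaboration and data sharing), and the Discussion admits that its duration is limited. If EC incidence is assumed to be 20 to 100 per 100,000 per year, the 100 PCOS and 100 endometriosis cases would yield 200 × 0.0002 = 0.04 to 200 × 0.001 = 0.2 EC cases a year. The enrolled EC group is the more realistic source of EC outcomes.

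Second, the shared rule describes the reason for surgery. A woman operated on for another condition may have past or incidental endometriosis. This stands: a reader might infer that exposure among EC controls is zero by construction, but the text supports depletion only, so f may be below 1.

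Third, a reader might infer that PCOS is screened out as well. The shared rule does not say so. The general sentence can be read as barring all four conditions from every control, or as introducing rules that apply condition by condition. Only the first reading extends the problem to PCOS.

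Fourth, a common surgical source is a sensible choice when control biopsies are hard to obtain, as Blood and tissue acknowledges, and Clinical data provides for recording history and diagnosis. Both are fair. Neither requires EC controls to be selected against endometriosis, and recorded history cannot restore women who were never enrolled.

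**Conclusion.** The point holds in a limited form. Followed as written, the shared rule yields EC controls depleted of endometriosis while EC cases are not, so they are unsuitable for estimating the endometriosis–EC association. The inflation factor is 1/(1 − f), with f unknown; the size therefore rests on an assumption, while the upward direction follows from the rule if controls are otherwise representative.

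A reader might go further and conclude that every EC case-control comparison is biased away from the null. The documents and the arithmetic do not support that. Factors unrelated to endometriosis are untouched, related ones can shift either way, and the other named EC use, genetic profiling of inherited cases, is not shown to be harmed. Participation rates and the other feasibility estimates are unaffected.

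**What to change.** Split the shared rule in two. Define EC controls as women having gynaecological surgery for benign conditions who do not have EC, whether or not they have endometriosis or PCOS, and record both conditions for EC cases and controls alike. Keep the no-endometriosis condition for the endometriosis controls only. Reword the general sentence so that each control group must be free of its own index condition, which also settles the PCOS ambiguity.

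This changes two sentences of eligibility text. The cost is that the EC and endometriosis control pools are no longer fully interchangeable. That is small, because Sample size already plans an equivalent number of controls for each group.

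If the shared pool is kept for practical reasons, state that these EC controls will not be used for the endometriosis–EC question, and do not count them towards sample sufficiency for that baseline study.

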#### Exclusion criteria

The study will exclude the following women. Non-residents in Dubai as they are less likely to be available for long-term follow-up, pregnancy (for the PCOS, endometriosis and EC aspects), younger than 18 years, and those unable to provide consent.

#### Participant recruitment

Institutional review board (IRB) approval from the MBRU IRB in Dubai was obtained in February 2025 (MBRU IRB-2024-692). In collaboration with gynaecologists, obstetricians, oncologists, and other healthcare providers (nurse or physician) eligible women will be identified and approached by an on-site trained research assistant with an information sheet detailing the project. Diagnosis will be based on the clinical diagnosis made by the physician supported by the relevant ICD-10 code. In women with PCOS, this will be verified by the Principal Investigators of the study, given previous research demonstrating disparity between physician and electronic health record diagnosis of PCOS and objective diagnosis using the Rotterdam, National Institutes of Health (NIH) or androgen excess and PCOS (AE-PCOS) criteria (40). Pre-eclampsia will be defined as the onset of a new episode of hypertension during pregnancy, characterized by persistent hypertension (diastolic blood pressure ≥90 mm Hg) and substantial proteinuria (>0.3 g/24 h or more or protein level of +2 or above in the urine dipstick test) (23).

If women express interest to participate, written informed consent will be obtained. This consent will include permission for follow-up interviews, extraction of health information from medical records, collection, and long-term storage of biospecimens and future research into the mechanisms of disease (including genetics) in the health conditions of interest and assurance of confidentiality. The broad consent model supports the collection of specimens and data for future, unspecified use within a broad set of parameters (24). The study will be conducted in accordance with the principles of the Declaration of Helsinki (25). Each participant will have the right to withdraw from the study at any time without giving any reason. During enrolment, the participant will be provided with a detailed information sheet on the study description, contact details of the research team (telephone number and email address) and the withdrawal process.

